## Abstract

**Background:**

Arthroscopic partial meniscectomy has been shown to be of no benefit to patients with concomitant knee osteoarthritis, but the optimal treatment of a degenerative meniscus tear in patients with mild or no knee osteoarthritis is unknown. This article describes the rationale and methodology of a randomized sham-controlled trial to assess the benefit of arthroscopic partial meniscectomy of a medial meniscus tear in patients with mild or no knee osteoarthritis. The objective of the study is to test whether the benefit from arthroscopic partial meniscectomy in patients with knee pain, medial meniscus lesion and mild/no knee osteoarthritis, is greater after arthroscopic partial meniscectomy than following sham surgery.

**Methods:**

We will conduct a randomized controlled trial of treatment for degenerative meniscus tears in middle-aged patients (aged 35–55 years) with an MRI-verified medial meniscus lesion and mild or no knee radiographic osteoarthritis (grade 0–2 on the Kellgren & Lawrence scale). Patients will be randomized to receive either conventional arthroscopic partial meniscectomy or a sham surgery procedure. The primary outcome will be the KOOS_5_ derived from the ‘*Knee Injury and Osteoarthritis Outcome Score’* at 2 years follow-up. Secondary outcomes at 2 years will include all five individual subscales of the KOOS, a global perceived effect score, the Short-Form-36 health status score, EQ-5D for economic appraisal and objective tests of muscle strength and physical function. Radiographic knee osteoarthritis will be evaluated at 5 years.

**Discussion:**

Demonstration of no additional benefit from arthroscopic partial meniscectomy on pain and function should lead to a change in clinical care of patients with a degenerative meniscus tear. The results of this study will provide empirical evidence for the potential benefit/harm of arthroscopic partial meniscectomy compared to a masked sham-therapeutics intervention.

**Trial registration:**

NCT01264991

## Background

A degenerative meniscus tear can be both a risk factor for knee osteoarthritis (OA) and a sign of disease [1]. The current standard treatment for a degenerative meniscus tear is arthroscopic partial meniscectomy (APM), the most commonly performed orthopedic procedure, carried out on 1 million patients annually in the USA [2]. Both meniscus injury and a meniscectomy are associated with the development of knee OA [3-5]. Previous studies have found APM to be no better than, or have no additional benefit in comparison to, sham surgery, lavage, optimized non-surgical treatment, or exercise [6-8]. In all these studies, patients with knee OA were included and the mean ages ranged from 52 to 62 years. The benefit in a younger population from an APM procedure in a knee with a degenerative meniscus tear and mild or no knee OA is, however, uncertain and needs to be further investigated.

The benefits of the APM procedure on pain and function in patients with a degenerative meniscus tear, were firstly described in non-controlled studies from the 1980s to the 1990s [9-11] when arthroscopic procedures were gaining acceptance. However, poorly designed studies (retrospectively, use of non-validated outcome measures, small patient populations, lack of control groups and randomized allocation) have prevented firm conclusions about the effect of the APM procedure. A previous, but now withdrawn, Cochrane review from 2000 [12] concluded: *”…lack of randomized trials means that no conclusions can be drawn on the issue of surgical versus non-surgical treatment of meniscus injuries”.* At the time of this submission, there are, to our knowledge, no published high quality controlled, randomized studies that show a benefit from APM as compared to other treatment modalities (placebo, physiotherapy, medication or exercise) on pain and function in patients aged 35–55 years with a degenerative medial meniscus tear.

Both meniscus injury and meniscectomy are associated with a high risk of knee OA. Surgical resection of the meniscus leads to increased joint cartilage contact stress through altered load transmission, decreased shock absorption, and decreased joint stability [13]. Of patients who undergo either total or partial meniscectomy, 50% on average develop knee OA within 10–20 years [5]. In the elderly population in general, and in patients with radiographic knee OA but no surgery, there is a higher incidence of MRI-verified concomitant meniscus injury compared to controls [4]. It remains unclear though, whether meniscectomy increases the risk of knee OA *per se*, compared to non-surgical treatment of a meniscus injury. In this study, incidence or progression of radiographic OA will be assessed at 5 years.

## Methods

### Study design

The study is designed as a prospective double-blind randomized sham-controlled, multi-centre trial (RCT). Patients will be randomly allocated to receive either an APM or sham (i.e. placebo) procedure. The study is designed according to current international standards and will be reported using the recommendations in the CONSORT statement [14]. The study is approved by the Research Ethics Committee of Region Zealand, Denmark, and is consistent with the Declaration of Helsinki.

Eligible patients will be screened using standardized fixed flexion radiography of both knees, to assess the degree of radiographic knee OA. If no, or at most mild, knee OA on radiographs (Kellgren & Lawrence grades 0–2) is present, written information about the study and a 10-minute information video will be given to the patients to view at home. They will also be handed a Patient-Reported Outcomes (PRO) questionnaire to fill out at home to minimize bias. At the second contact, the patients will receive an MRI scan of the affected knee and perform tests of physical function. Thereafter, the relevant researcher and the patient will be informed of the MRI findings. If the MRI confirms a medial meniscus lesion, the patient will be invited to participate in the study. Patients not consenting to randomization will be followed as an observational cohort with consecutive PRO evaluation at the same time points as those included in the RCT. However, the observational cohort will not be part of the Intention-To-Treat (ITT) population.

At 3 months, patients will have a clinical examination, fill out PRO questionnaires, and perform objective tests of muscle strength and physical function. At 2 years, follow-up will take place under the same conditions. At 5 years, all patients will have radiography of their knees to assess possible onset or progress of knee OA from baseline. The flowchart provides a visual description of the study (Figure 1).

**Figure 1 F1:**
[figure not shown]
Study flowchart.

### Purpose and hypothesis

The purpose of the present study is to determine whether the benefit from arthroscopic partial meniscectomy in patients aged 35–55 years with knee pain and an MRI-verified medial meniscus lesion, is greater after arthroscopic partial meniscectomy than following sham surgery. In addition, a 5-year follow-up of the same cohort will compare the effect of meniscectomy or sham surgery on the incidence and progression of radiographic knee OA.

We hypothesize that at 2 years, the change (improvement) in KOOS_5_, a composite score derived from the five subscales of the KOOS, is no greater after APM than following sham surgery. Further, we hypothesize, that at 5 years the rate of radiographic knee OA incidence and progression is greater in the APM group than in the sham surgery group.

### Participants

Eligibility criteria are patients between 35 and 55 years of age with knee pain for more than 2 months without significant trauma and an MRI-confirmed medial meniscus lesion. The patients must be eligible for outpatient surgery. Patients will be excluded if they are in need of acute surgery e.g. locking knees or high-energy trauma. Patients with grade 3 or 4 knee OA on the Kellgren & Lawrence classification [15,16] or knee surgery within the previous 2 years will also be excluded. Patients must be able to speak Danish and be free of any drug or alcohol abuse. Also, patients with trombophilia are excluded so as to prevent a high risk of deep venous thrombosis. The patients will be recruited through outpatient departments of the orthopedic clinics in Region Zealand on referral from general practitioners.

### Interventions

Patients will be randomized to receive either arthroscopic partial meniscectomy (intervention A) or placebo procedure/sham surgery (intervention B).

### Intervention A

The arthroscopic partial meniscectomy will be performed on an outpatient basis by experienced surgeons who are at least in their final year of residency or are attending orthopedic surgeons. We expect between 5–10 surgeons to be involved in the study. All arthroscopies will be performed with general anesthesia combined with local anesthesia (Bupivacain combined with Adrenalin) 20 + 20 ml extra- and intra-articularly, respectively. After general anesthesia is induced, the knee will be examined for stability. Thereafter, two standard portals on the lateral and medial sides of the ligamentum patella will be created but no outflow cannula inserted. An arthroscope will be used with a pressure-controlled irrigation system. Tourniquet use will be at the discretion of the surgeon. The strategy for the meniscectomy will be to preserve as much tissue as possible. A standard operation protocol will be used to document possible findings in cartilage, ligaments, synovium and the medial and lateral menisci. The type, and extent of meniscus lesion will be registered and changes in the articular cartilage will be classified according to the ICRS classification [17].

### Intervention B

The sham procedure will be performed under the same conditions as the arthroscopic surgery (Intervention A). In summary, the patient will be fully sedated with general anesthesia and the stability of the knee will be examined. Local anesthetic will be applied and two skin incisions will be made at the same locations and of the same size as in Intervention A. Then the knee will be manipulated as if a real arthroscopy was performed, the spillage of water and all other equipment needed for an arthroscopy will be used. A pre-recorded video of a standard arthroscopic partial meniscectomy will be played during the procedure. No instruments will enter the arthroscopy portals to avoid the possibility of deep infection, osteochondral lesions or unwanted interventions by the surgeon.

### Postoperative regime (independent of concealed group allocation)

All patients in both intervention groups will be given a folder including an exercise program for postoperative patients after knee arthroscopy. The folder gives a presentation of seven different non-weight bearing exercises (for the first week after surgery) and a further three weight-bearing exercises thereafter. The exercises are for the patients to carry out at home. The patients are also recommended to start unloaded cycling, swimming or walking after 1 week, and jogging or loaded cycling after 2–3 weeks.

### Primary outcome

All outcomes are listed in Table 1. The primary outcome at 2 years follow-up will be KOOS_5_, a composite score derived from the *Knee injury and Osteoarthritis Outcome Score* (KOOS) [18,19]. The KOOS is a self-reported questionnaire comprising five subscales: pain, other symptoms, activities in daily living (ADL), function in sport and recreation and knee-related quality of life (QOL). The previous week is taken into consideration when patients are answering the questions. Standardized answer options are given (5 boxes on a Likert scale) and each question gets a score from 0 to 4. A normalized score (100 indicating no symptoms and 0 indicating extreme symptoms) is calculated for each subscale.

**Table 1 T1:** Summary of measures to be collected

**Variable**	**Baseline**	**Intermediate**	**Primary endpoint**	**Follow-up**
	**T = 0 mths**	**T = 3 mths**	**T = 2 yrs**	**T = 5 yrs**
** *Baseline data* **				
Age – [contact].	n.a.	n.a.
Female sex - no. (%)	@	n.a.	n.a.	n.a.
Duration of knee symptoms - [contact].	n.a.	n.a.
Height - [contact].	n.a.	n.a.
Body weight - [contact].	@	@
Self-efficacy [contact].	n.a.	n.a.
** *Knee injury and Osteoarthritis Outcome Score (KOOS)* **				
Pain – range: 0-100	@	@	@	@
Symptoms - range: 0-100	@	@	@	@
Function in daily living – range: 0-100	@	@	@	@
Function in sport and recreation – range: 0-100	@	@	@	@
Knee related Quality of life – range: 0-100	@	@	@	@
** *EQ-5D* **				
Global disease descriptive system	@	@	@	@
VAS patient global assessment of disease status - 0-100	@	@	@	@
** *Short-Form-36 health survey - acute form* **				
Physical component summary – range: 0-100	@	@	@	@
Mental component summary – range: 0-100	@	@	@	@
** *Global Perceived Effect* **				
7 step scale ranging from much worse to much better	n.a.	@	@	@
** *Standardized knee radiographic with SynaFlexer* **				
JSW and presence of [contact]	n.a	@
** *Performance measures* **				
Single leg hop test	@	@	@	n.a.
Knee-bending test	@	@	@	n.a.
Isometric knee extensor strength	@	@	@	n.a.

@ = Assessed; n.a. = not assessed; VAS = Visual Analogue Scale; JSW = joint space width.

Subsequently, KOOS_5_ is calculated as a mean of the 5 subscale scores [KOOS_pain_ + KOOS_symptoms_ + KOOS_ADL_ + KOOS_sport &rec_ + KOOS_QOL_]/5.

### Secondary outcomes

#### KOOS

All five subscales from the KOOS will be included individually as secondary outcomes to support a clinically valid interpretation of the result.

#### Global perceived effect

All patients are asked to answer on a seven-step global rating scale (ranging from much worse, worse, slightly worse, no difference, slightly better, better to much better) the overall improvement in their knee symptoms after the operation. This is implemented to determine the minimal important change in the PROs. A clinically important change is considered when the patient reports an improvement or worsening of at least 2 steps from ‘no difference’, corresponding to ‘better’ or ‘worse’ on the scale [20].

#### Generic patient reported outcomes

Scores on the Medical Outcomes Study 36-item Short-Form General Health Survey (SF-36) [21,22], which reflect the health-related quality of life (SF-36 Health Survey) – Acute version (1 week re-call period) will be used as a generic measure of patient health status at 3 and 24 months. The SF-36 is comprised of 8 single subscale scores associated with physical and mental health.

The Euroqol 5 Dimension (EQ-5D) health score will be evaluated at baseline and at 3 and 24 months as a generic measure for economic appraisal [23,24]. EQ-5D consists of two pages - the EQ-5D descriptive system and the EQ visual analogue scale (EQ VAS). The EQ-5D descriptive system comprises the following 5 dimensions: mobility, self-care, usual activities, pain/discomfort and anxiety/depression. Each dimension has 3 levels: no problems, some problems, severe problems.

#### Performance measures

Tests of physical function will be performed at baseline and after 3 and 24 months including a one-leg jump test, maximum number of knee bends in 30 seconds and an isometric knee extension strength measurement. The patients will wear shorts, t-shirts, and sneakers. Tubigrip stockings will cover both knees to disguise scars from surgery; i.e., the test leaders will be masked regarding injured knee. In order to avoid bias from the effect of learning, randomization will be performed at each visit to determine which leg is to be tested first.

#### Single leg hop test

The one-leg hop will be included as a measure of physical function at a level above activities of daily living [25]. The one leg hop requires leg muscle strength, knee stability and confidence in knee function [26]. Subjects will perform two practice trials and then three test trials on each leg with hands behind their back. The best of the three test trials will be used. An additional trial will be performed if the patients improve more than 10 centimeters from trial two to trial three [27].

#### Knee-bend test

The maximum number of knee-bends performed in 30 seconds will be included as a measure of one-legged physical function required in daily life. This test requires fast changes between concentric and eccentric work and resembles stepping down a stair and is valid and reliable in meniscectomized patients [27].

#### Isometric knee extensor strength

Maximum knee-extension force will be measured using a hand-held dynamometer (Powertrack Commander). Patients will sit at the end of the examination couch with hip angle at 90° and knee angle at 60°. A large Velcro strap will be attached to the examination couch and the patient’s ankle will be perpendicular to the lower leg. The transducer will be placed at the front of the ankle under the Velcro strap to measure knee extension force. Patients will be instructed to contract “as forcefully as possible” with a gradual increase in force and strong verbal encouragement will be provided during the contractions. They will perform 3 contractions separated by a 60-second pause, and the highest value will be used as the result.

The reliability of the isometric muscle tests with a hand-held dynamometer has been reported to be satisfactory [28-30]. The knee extension strength will be expressed as maximal voluntary torque per kilo of body mass using the external lever-arm length and body mass of each patient.

#### Radiographic OA

To evaluate progression of knee OA, a fixed-flexion radiography procedure, with use of SynaFlexer [31], will be performed at baseline and after 5 years. This provides radiography at the exact same position and has been validated in determining joint space width (JSW) in knee osteoarthritis [32]. A single reader will score all the study films from baseline and 5-year follow-up and will be blinded to all clinical and questionnaire data and the baseline x-ray result but not to the sequence of the x-rays. A score will be assigned to each x-ray based on JSW and presence of osteophytes using a standard atlas [33].

### Exploratory outcomes

A questionnaire of patient self-efficacy modified from the Danish Arthritis Self-Efficacy Scale to suit this somewhat younger age group (not formally validated) and a question on patient expectations will be included. Demographic data will also be collected. Furthermore, participating patients will be asked two questions regarding their study participation. 1) “Which reason is the most motivating for your participation?” and 2) “Which information was the most useful when deciding?” Physical therapy prescribed by either a general practitioner or a research staff member will be carefully monitored with regard to the number of exercise sessions.

### Adverse events

Adverse events (not necessarily implying causality) will be registered in both treatment arms. A priori defined adverse events are: superficial infection, nerve or vessel injury, deep infection, compartment syndrome, deep venous thrombosis, myocardial infarction, stroke, and death. Re-arthroscopy is also considered an adverse event. Adverse events will be gathered from patients themselves, from the patient record review, and from the Danish National Patient Index (NPI) at the 3 and 24 months follow-ups.

### Sample size

The sample-size calculation is based on the assumed superiority of the arthroscopic procedures over the sham procedure. For a two-sample pooled t-test of a normal mean difference with a two-sided significance level of 0.05, assuming a common standard deviation (SD) of 15 in the KOOS_5_ score, a sample size estimation of the ITT population indicated that 36 individuals per group would be required to obtain a power of at least 80% to detect a minimal important change (MIC) of 10 KOOS_5_ score units. The MIC of 10 points and SD of 15 is based on findings from similar patient groups and interventions [19].

Following these estimations, it was decided to include 80 individuals in total (40 patients in each group), allowing for a 10% drop-out rate.

### Randomization

We will generate the two comparison groups using simple randomization, with an equal allocation ratio (1:1), by referring to a computer-generated table of random numbers. To ensure an equal distribution in the two groups, we will use a block randomization, using blocks of 4 and 6. Participants will be stratified for treatment centre. To ensure concealment of the assigned intervention, the surgeon will obtain a sealed envelope containing the participant’s assigned intervention after the patient is in the operating suite and has been fully sedated. The consecutively numbered envelope will be retrieved from a briefcase located at the actual operating theatre. The above mentioned allocation sequence will be generated by an external co-investigator, the enrolment will be performed by the first author and the assignment will be at the operating room where the envelope will be opened by the surgeon.

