### Blinding

The RCT will be a double-blind trial. All study personnel and participants will be blinded to the intervention, except for the surgeons and other operating theatre personnel, who do not have any other role in the study.

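### As the Randomization section reads, allocation follows operating order from small blocks within centre, so unblinded theatre staff can guess the next allocation better than chance

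*Protocol article*

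**What the plan says.** The protocol article, Methods, Randomization, fixes these elements:

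- Sequence: "we will use a block randomization, using blocks of 4 and 6", at a 1:1 ratio, and "Participants will be stratified for treatment centre". An external co-investigator generates it.
- Timing: the surgeon obtains a sealed envelope "after the patient is in the operating suite and has been fully sedated".
- Source: "The consecutively numbered envelope will be retrieved from a briefcase located at the actual operating theatre".
- Place of assignment: enrolment is done by a researcher who is not the operating surgeon, and "the assignment will be at the operating room where the envelope will be opened by the surgeon".

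The same section opens by naming a different method: "We will generate the two comparison groups using simple randomization, with an equal allocation ratio (1:1".

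The Blinding section masks everyone "except for the surgeons and other operating theatre personnel, who do not have any other role in the study". Intervention A expects 5–10 surgeons. Study design describes a multi-centre trial, but the number of centres is not given. Sample size sets 80 patients in total.

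**The concern.** Assignment is placed in theatre, and the envelopes are used in numerical order. The section describes no earlier link between a patient and a number. So the next trial patient to be anaesthetised at a centre receives the next allocation in that centre's sequence.

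The people present at that moment are also the people who see allocations. Sham is staged in theatre (Intervention B), so everyone in the room learns which arm was given. With short balanced blocks, past allocations carry information about the next one, and using that information does not require opening any envelope early.

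Allocation concealment would be at stake. If someone could both guess the next allocation and change which trial patient comes next, patients with a particular outlook could be placed in a particular arm. An analysis by randomized group would not repair that. The Discussion describes partial meniscectomy as the current treatment of choice for these patients, so a preference among surgeons is not far-fetched.

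**Working it through.** The article gives no figure for predictability, so there is none to reproduce. Its sample size is not in dispute: 2 × (1.96 + 0.84)² × 15² / 10² ≈ 35.3, rounded up to the stated 36 per group. Nothing below changes it.

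**Inputs from the article:** blocks of 4 and 6, 1:1, within centre; 80 patients; 5–10 surgeons.

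**Assumptions, because the article is silent:**
- The two block sizes come in random order with equal probability.
- The observer knows that the sizes are 4 or 6 and always makes the best guess.
- Each earlier allocation at the centre is known with a probability of 100%, 50%, 20% or 10%. One of five surgeons sharing a sequence equally would know about 20%, and one of ten about 10%.
- A centre has 80, 40 or 20 patients.

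**Step 1. All earlier allocations and the block boundaries known (exact).** Take a block with *m* patients per arm.
- Share of allocations that are certain: 1/(m + 1). Block of 4 (m = 2): 1/3 = 33%. Block of 6 (m = 3): 1/4 = 25%.
- Expected correct guesses per block: m + 2^(2m−1)/C(2m, m) − 1/2. Block of 4: 2 + 8/6 − 0.5 = 2.833, and 2.833/4 = 71%. Block of 6: 3 + 32/20 − 0.5 = 4.1, and 4.1/6 = 68%.
- Equal mix of the two sizes: certain (4 × 1/3 + 6 × 1/4)/10 = 28%; correct (2.833 + 4.1)/10 = 69%.

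Full enumeration of the blocks gives the same values for each size.

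**Step 2. Boundaries unknown (simulation).** The observer updates the probability of each possible block state after every patient. There were 800, 1,600 and 3,200 runs for centres of 80, 40 and 20 patients.

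| Earlier allocations known | Best guess correct (centre of 80 / 40 / 20) | Next allocation certain (80 / 40 / 20) |
|---|---|---|
| 100% | 69.1% / 68.9% / 68.6% | 5.5% / 5.6% / 5.8% |
| 50% | 58.8% / 58.5% / 58.2% | 0.2% / 0.3% / 0.4% |
| 20% | 54.2% / 54.1% / 53.9% | 0.0% in each |
| 10% | 52.2% / 52.3% / 52.2% | 0.0% in each |

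With everything known, one arm has a probability of at least 75% for 49%, 48% and 46% of patients respectively. With half known, that falls to about 7%.

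**Step 3. Reading the results.** Centre size hardly matters. The share of earlier allocations known matters most. Knowing the boundaries adds almost nothing to the rate of correct guesses (69% either way), but raises the certain allocations from about 6% to 28%. Mixing two block sizes therefore does useful work, though it leaves a better-than-chance guess.

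**The case against.** The strongest reply is that harm needs a chain of conditions, most of which the article does not state. Someone must track past allocations, know the block sizes, control the schedule, and have at least two trial patients to reorder. The Blinding section gives theatre personnel no other role in the study, and enrolment belongs to someone else. The sequence is external, the envelopes are sealed and numbered, and late opening also avoids withdrawals between randomization and surgery. A better guess is not in itself selection bias, and no figure here shows bias in KOOS5.

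Much of this stands. A reader might infer that the surgeon knows every earlier allocation. The article does not say so: with 5–10 surgeons, each is sure to know only the envelopes he or she opened, and 69% is the upper end of the range. A reader might also infer that surgeons steer allocation through the operating list. The article does not say who sets the order, or whether trial patients ever share a list.

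Two parts do not stand. First, the safeguards protect mainly against bias at enrolment and against early opening. None stops prediction from past allocations, and none fixes patient order before theatre. Second, this is not merely detail left to a fuller document. The text can be read as meaning an envelope already made out to a given participant, but it expressly puts assignment in the operating room and describes no earlier link. Whether block sizes are withheld from surgeons is the kind of detail an article omits, and it is not raised here.

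**Conclusion.** The point holds as a conditional weakness in a stated mechanism, worth correcting but not fatal. As written, allocation follows operating order, and unblinded theatre staff with knowledge of earlier allocations can beat chance. The range is about 52–59% correct with 10–50% of earlier allocations known and about 69% with all known. At most about 6% are certain, or 28% if the block boundaries are known too.

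These figures rest on the assumed random order of block sizes and on an observer who knows the sizes are 4 or 6; one who does not could do no better. They measure predictability, not bias in the treatment effect. Steering is possible only if theatre staff can influence the order or timing of trial patients, and the article leaves that open.

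The simple-randomization label contradicts the blocks and stratification that follow it. The intended method is clear from those sentences, so this is an editorial matter and adds nothing to the concern about predictability.

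**What to change.** In Randomization, state that the enrolling researcher, who is blinded, links the centre's next consecutive envelope number to the patient at enrolment, before the operation date is set. Only the envelope bearing that patient's number may be opened in theatre, whatever the order of operations. Changing the order then no longer changes who gets which allocation, even if the allocation can be guessed.

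Keep randomization defined as the opening of the envelope after sedation. Statistical methods analyses all randomized individuals. Without this definition, patients who withdraw between linking and surgery could be counted as randomized but untreated, which the present procedure avoids.

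As an editorial correction, replace the reference to simple randomization with permuted-block randomization stratified by centre.

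The cost is a sentence or two and a number on each envelope. Patients who withdraw before surgery leave a few unopened envelopes and slightly incomplete blocks. Because withdrawal before opening would be the remaining route for selection, a log of unopened numbers with reasons is worth keeping. The sample size does not change.
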